## 5.5. EVALUATIONS DURING TREATMENT

The following assessments will be done while the patient is on treatment.

Table. Evaluations during treatment

|                                         | ASSESSMENT                                                                                                                                                                                                                                                                                                     | TIME                                                                                                                                                                                                                                                                                                                                                                                                                                         |
|-----------------------------------------|----------------------------------------------------------------------------------------------------------------------------------------------------------------------------------------------------------------------------------------------------------------------------------------------------------------|----------------------------------------------------------------------------------------------------------------------------------------------------------------------------------------------------------------------------------------------------------------------------------------------------------------------------------------------------------------------------------------------------------------------------------------------|
| 1. Clinical examination          | 
 
Complete physical examination
 
Performance status (ECOG PS; see Appendix 1)
 
                                                                                                                                                                          | Day 1 of cycle 1
Repeat on Day 15 of Cycle 1
Repeat on Days 1 and 15 of cycle 2
Repeat on Day 1 of each subsequent cycle
At discontinuation visit                                                                                                                                                                                                                                                                                |
|                                         | 
 
Vital signs: heart rate, blood pressure, body temperature and weight
 
                                                                                                                                                                                         | Day 1 of cycle 1
Repeat on Day 15 of Cycle 1
Repeat on Days 1 and 15 of each subsequent cycle
At discontinuation visit                                                                                                                                                                                                                                                                                                              |
|                                         | 
 
Assessment of signs and symptoms
 
                                                                                                                                                                                                                             | Throughout the treatment period                                                                                                                                                                                                                                                                                                                                                                                                              |
|                                         | 
 
Concomitant diseases and treatments
 
                                                                                                                                                                                                                          | Throughout the treatment period                                                                                                                                                                                                                                                                                                                                                                                                              |
| 2. Laboratory tests*             | 
 
Hematology: neutrophils, lymphocytes, basophils, eosinophils, monocytes, haemoglobin, platelet count, red blood cell count, total white cell count.
 
                                                                                                   | Up to 24 hours before Day 1 of cycle 1
Repeat on Days 8, 15 and 22 of Cycles 1 and 2
Thereafter, repeat before each Avelumab injection (ie. Day 1 and Day 15).
At discontinuation visit                                                                                                                                                                                                                                             |
|                                         | 
 
Biochemistry: Serum electrolytes (Na+, K+, Cl, P and Ca++), liver function tests (AST, ALT, total bilirubin, GGT and AP), LDH, creatinine, glucose, total proteins, urea, albumin, CPK, lipase, amylase.
 
 | Up to 24 hours before Day 1 of cycle 1
Repeat on Day 15 of Cycle 1
Repeat before each Avelumab injection (ie. Day 1 and Day 15).
At discontinuation visit
Note that hepatic tests (AST, ALT, GGT and alkaline phosphatase) must be also performed at Days 8 and 22 of cycles 1 and 2                                                                                                                                      |
|                                         | 
 
Thyroid test: 
 
All cohorts : TSH,
 
For cohort F only : Thyroglobulin and Antithyroglobulin antibody
 
 
 
                                                                                         | Up to 24 hours before Day 1 of cycle 1 
 
All cohorts : TSH : Repeat on Day 15 of Cycle 1, repeat on Day 1 and Day 15 of cycle 2, then on Day 1 of each subsequent cycle, at discontinuation visit and safety follow-up visit
 
For cohort F only : Thyroglobulin and Antithyroglobulin antibody : repeat on Day 1 every 2 cycles, at discontinuation visit and safety follow-up visit
 
 |
|                                         | 
 
Coagulation: TP, INR, aPTT
 
Urinary: blood, glucose, protein, gravity (dipstick)
 
                                                                                                                                                       | Up to 24 hours before Day 1 of cycle 1
Repeat on Day 15 of Cycle 1
Repeat on Day 1 and Day 15 of cycle 2.
Repeat on Day 1 of each subsequent cycle
At discontinuation visit                                                                                                                                                                                                                                                      |
| 3. Creatinine clearance          | 
 
Calculated using the Cockcroft formula (see Appendix 2)
 
                                                                                                                                                                                                      | Up to 24 hours before Day 1 of cycle 1
Repeat on Day 15 of Cycle 1
Repeat on Days 1 and 15 of cycle 2.
Repeat on Day 1 of each subsequent cycle
At discontinuation visit                                                                                                                                                                                                                                                         |
| 4. Pregnancy test, if applicable | 
 
Measurement of serum human chorionic gonadotropin (HCG)
 
                                                                                                                                                                                               | To be repeated within 72 hours prior to the start of study treatment.
Will be repeated on day 1 of each cycle, in women with childbearing potential                                                                                                                                                                                                                                                                                       |
| 5. ECG                           | 
 
Electrocardiogram
 
                                                                                                                                                                                                                                            | If clinically indicated                                                                                                                                                                                                                                                                                                                                                                                                                      |
| 6. Tumor assessment              | 
 
CT scan or MRI of all measurable sites, as per RECIST (see Appendix 3)
 
                                                                                                                                                                                       | Tumor assessment must be repeated every eight weeks ( $\pm 7$ days) and at least four weeks after first documentation of objective response even if there are treatment delays.                                                                                                                                                                                                                                                              |
| 7. PK study                      | 
 
Blood samples
 
                                                                                                                                                                                                                                                | For phase I only, see section 17.1                                                                                                                                                                                                                                                                                                                                                                                                           |

|                           | ASSESSMENT                                                                                           | TIME                                                                                                                                                                                                            |
|---------------------------|------------------------------------------------------------------------------------------------------|-----------------------------------------------------------------------------------------------------------------------------------------------------------------------------------------------------------------|
| 8. Biomarker study | 
 
♦ Blood samples
 
♦ Stool sample (optional)
 
 | See section 17.2 
 
♦ Blood samples at C1D1, C2D1, C4D1, C6D1 and at progression (pre-dose).
 
♦ Stool sample for the microbiota only at C1D1 (pre-dose).
 
 |
| 9. Biopsy          | 
 
♦ Only for consented patient (optional)
 
            | At cycle 2 Day 1, after 4 weeks of treatment.
For more details, please refer to section 17.3                                                                                                                 |
| 10. AEs            | As per NCI-CTCAE, version 5.                                                                         | Throughout the treatment period                                                                                                                                                                                 |

\*For all laboratory tests a window of 72 hours will be allowed.

## 5.6. EVALUATION AT SAFETY FOLLOW-UP VISIT

The safety follow-up will be scheduled 30 days (4 weeks) after the last treatment administration (a window of  $\pm 1$  week is allowed). In case of the patients starts a new antitumor therapy, this visit must be done before the date of administration of this new antitumor therapy.

Regardless of the reason for discontinuation, the complete workup has to be done at the end-of-treatment visit. This will include the following assessments:

- Assessment of signs and symptoms.
- Complete physical examination.
- ECOG performance status.
- Vital signs [heart rate, blood pressure, and temperature].
- Hematology.
- Biochemistry.
- Thyroid function.
- Urinalysis.
- Calculated CrCl.
- Clinical and radiological tumor assessment (MRI) (except for patients with confirmed PD at discontinuation or who had started a new treatment).
- Intercurrent events and concomitant disease and treatments.
- Safety assessment (AEs).

Adverse events and SAE must be reported for 30 days after the last treatment administration or until the start of a new antitumor therapy, whichever occurs first. Note that even if the patient has started a new antitumor therapy, all AE and SAE suspected to be treatment-related will be reported until 30 days after the last treatment administration.

**Moreover, extended safety follow-up (ESFUP)** must be performed up to 90 days after the last dose of avelumab administration (ie. 60 days after SFUP). This visit may be performed either via a site visit or via a telephone call with subsequent site visit requested in case any concerns noted during the telephone call. Beyond this period of time, only those SAEs suspected to be treatment-related will be reported (see Section 11).

## 5.7. FOLLOW-UP

- The date and reason of the study discontinuation will be recorded on the patient's CRF (see Section 5.2).
- Patients who discontinue treatment without PD will be followed every 12 weeks until progression, other antitumor therapy or death or until the date of study termination, whichever occurs first.
- After treatment discontinuation, patients will be followed every 6 months until death or until the date of study termination, whichever occurs first.
- Patients who withdraw consent will not be followed with any study procedures.

All AEs (including SAEs) suspected to be treatment-related or research-related will be followed-up until the events or their sequelae resolve or stabilize at a level acceptable to the Investigator and the Sponsor.

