## **5.2. DEFINITIONS OF DURATION OF STUDY AND TREATMENT (PER PATIENT)**

Patients will receive study treatment as long as it is considered to be in their best interest. Patients will be evaluated at scheduled visits in up to five study periods:

- **Pre-treatment (PRE TT):** from signature of informed consent to the first administration of study drugs.
- **Treatment (TT):** from the first administration of study drugs to treatment discontinuation
- **Safety follow-up (SFUP):** after treatment discontinuation, safety follow-up must be performed 30 days after the last treatment administration (toxicity assessment).
- **Extended safety follow-up (ESFUP):** given the potential risk for delayed immune-related toxicities, extended safety follow-up must be performed up to 90 days after the last dose of avelumab administration (ie. 60 days after SFUP). This visit may be performed either via a site visit or via a telephone call with subsequent site visit requested in case any concerns noted during the telephone call
- **Follow-up (FUP):**

After safety follow-up visit, patients who discontinue treatment without progression will be followed **every 12 weeks until:**

1. Disease progression,
2. Initiation of other antitumor therapy,
3. Death, or
4. The date of study termination, whichever occurs first.

After documented progression or start of a new antitumor therapy, patients will be **followed every 6 months until:**

1. Death, or
2. The date of study termination, whichever occurs first.

Patients will be considered to be **on-study** from the signature of the informed consent to the end of follow-up period.

Patients will be considered to be **on-treatment** for the duration of their treatment until 90 days after the last treatment administration, except if the patient starts a new antitumor therapy before this period. Patients may withdraw their consent at any time; no further study activities will be conducted on them.

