### 7.5.2. Prohibited concomitant medication

Subjects are prohibited from receiving the following therapies during the Screening and Treatment Phase (including retreatment for post-complete response relapse) of this trial:

- Anti-cancer systemic chemotherapy or biological therapy
- Chemotherapy not specified in this protocol
- Immunotherapy not specified in this protocol
- Investigational agents other than Avelumab and Regorafenib
- Live vaccines within 30 days prior to the first dose of trial treatment and while participating in the trial. Examples of live vaccines include, but are not limited to, the following: measles, mumps, rubella, varicella, zoster, yellow fever, intranasal influenza, rabies, BCG and typhoid vaccine.
- Current use of immunosuppressive medication, EXCEPT for the following:
  - Intranasal, inhaled, topical steroids, or local steroid injection (e.g., intra-articular injection);
  - Systemic corticosteroids at physiologic doses  $\leq 10$  mg/day of prednisone or equivalent; Higher doses can be used for the management of immune related adverse events and/or skin rash (see appendix 8).
  - Steroids as premedication for hypersensitivity reactions (e.g., CT scan premedication).
- The use of oral anticoagulation therapy (i.e. warfarin, acenocoumarol, phenprocoumon) is not permitted since warfarin is metabolized by CYP2C9 and CYP3A4. Low molecular weight heparin and heparin are allowed.

Subjects who, in the assessment by the investigator, require the use of any of the aforementioned treatments for clinical management should be removed from the trial. Subjects may receive other medications that the investigator deems to be medically necessary.

The Exclusion Criteria describes other medications which are prohibited in this trial.

There are no prohibited therapies during the Post-Treatment Follow-up Phase.

*Short course Radiotherapy* for symptoms or *palliative* treatment may be allowed after discussion with the sponsor.

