### **8.2.1. Assessing Objective Tumor Response (RECIST v1.1)**

- A comprehensive workup will be performed at baseline, and every 8 weeks.
- Whenever response criteria are met, the appropriate imaging tests should be repeated at least four weeks later in order to confirm the response.
- The same method will be used to evaluate each identified lesion both at baseline and throughout the study.
- Treatment will be administered as long as no disease progression or unacceptable toxicity is found, or as long as no other reasons for treatment discontinuation are met.
- Assessment of efficacy will be essentially based on a set of measurable lesions identified at baseline as target lesions and followed until disease progression and following the RECIST v1.1 criteria (Eisenhauer, 2009).

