### **8.2.2. Centralized Radiological Review (Institut Bergonié)**

#### **8.2.2.1. GENERAL PROCEDURE**

Centralized radiological review will be performed to confirm disease status under treatment in comparison with baseline, Week#8, Week #16, Week#24 and every eight weeks thereafter. For patients included in the reference center, CT scan will be initially read by a radiologist who differs from the expert. Review process will be centralized at Institut Bergonié and will be performed by a radiologist expert in solid and digestive tumors.

In case of discordance between the local radiologist and the expert reviewer, the judgment provided by the expert reviewer will be retained to continue or stop the treatment: treatment must be continued until central review response is available.

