- For cohorts B (GIST), H (NSCLC), I (Solid tumors -TLS+), M (TMB-high solid tumors), N (MSI-high solid tumors), O (non clear-cell renal carcinoma) and P (malignant pleural mesothelioma), antitumor activity will be assessed in terms of 6-month progression-free rate (6-month PFR) based on RECIST 1.1 criteria after in-stream centralized radiological review. 6-month PFR is defined as the proportion of patients with progression-free status at 6 months. Progression-free status is defined as complete response (confirmed or unconfirmed), partial response (confirmed or unconfirmed) or stable disease more than 24 weeks as defined as per RECIST v1.1 criteria.
- For cohort A' with immune signature (based on low tumor-associated macrophages infiltrate level) antitumor activity will be assessed in terms of 4-month progression-free rate (4-month PFR) based on RECIST 1.1 criteria after in-stream centralized radiological review. 4-month PFR is defined as the proportion of patients with progression-free status at 4 months. Progression-free status is defined as complete response (confirmed or unconfirmed), partial response (confirmed or unconfirmed) or stable disease more than 24 weeks as defined as per RECIST v1.1 criteria.
- For cohorts J (Urothelial cancer), K (HPV-associated cancer) and L (Triple negative breast cancer): antitumor activity will be assessed in terms of disease control rate at 6-month (6-month DCR rate) based on RECIST 1.1 criteria after in-stream centralized radiological review. 6-month DCR rate is defined as as the proportion of participants with confirmed complete response (CR), unconfirmed complete response (CRu), confirmed partial response (PR) or unconfirmed partial response (PRu) or stable disease (SD), as per adapted RECIST v1.1, observed within 24 weeks of treatment onset (while treated with the investigational product).

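### The protocol's assessment schedules disagree once treatment stops without progression, so a week-24 scan for the 6-month PFR is not guaranteed

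*Protocol*

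**What the plan says.** All references are to the protocol.

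- **Off treatment.** Section 5.7: "Patients who discontinue treatment without PD will be followed every 12 weeks until progression, other antitumor therapy or death". Section 5.2 gives the same interval and its starting point: "After safety follow-up visit, patients who discontinue treatment without progression will be followed" every 12 weeks.
- **Safety visit.** Section 5.6 places it 30 days (±1 week) after the last administration and requires imaging then, unless progression is confirmed or new treatment has begun.
- **On treatment.** In the section 5.5 table of assessments during treatment, "Tumor assessment must be repeated every eight weeks" (±7 days). Section 8.2.2.1 has central review confirm status under treatment at "Week#8, Week #16, Week#24 and every eight weeks thereafter".
- **What counts as on treatment.** Section 5.2 extends it to 90 days after the last administration, unless a new antitumour therapy starts.
- **Efficacy workup.** Section 8.2.1: "A comprehensive workup will be performed at baseline, and every 8 weeks". No limit to the treatment period is stated.
- **Endpoint.** Section 9.2.1, for cohorts B, H, I, M, N, O and P: "6-month PFR is defined as the proportion of patients with progression-free status at 6 months". Stable disease must last more than 24 weeks. Section 10.3.2.2 counts patients alive and progression-free at 6 months, over all eligible and assessable patients.
- **New therapy.** Section 7.5.2: "There are no prohibited therapies during the Post-Treatment Follow-up Phase".

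**The concern.** The 6-month PFR depends on status at week 24. On treatment, scans at weeks 8, 16 and 24 settle it. Off treatment, sections 5.2 and 5.7 move the patient to a schedule that counts from the safety visit and need not include week 24. A tumour that grows before week 24 may first be seen after it, and the patient then meets the stable-disease criterion. Ascertainment of a primary endpoint would then depend on whether the patient tolerated the treatment. These are uncontrolled cohorts judged on a single count, so a few such patients can matter.

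**Working it through.** **1. When week 24 goes unscanned (12-weekly reading)**

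Let T be the week in which both drugs are last given. The safety scan falls at s = T + 30/7 = T + 4.3. The first 12-weekly visit falls at v = s + 12 = T + 16.3. Week 24 lies between them when s < 24 < v, that is 24 − 16.3 = 7.7 < T < 24 − 4.3 = 19.7.

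| Stop T | Safety scan | Next visit | Unscanned weeks before week 24 |
|---|---|---|---|
| 6 | 10.3 | 22.3 | next visit is before week 24 |
| 8 | 12.3 | 24.3 | 11.7 |
| 10 | 14.3 | 26.3 | 9.7 |
| 12 | 16.3 | 28.3 | 7.7 |
| 16 | 20.3 | 32.3 | 3.7 |
| 20 | 24.3 | 36.3 | 0 |

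At a 20% null rate with exponential progression, a patient stable at week 14.3 progresses by week 24 with probability 1 − 0.20^(9.7/24) = 0.48.

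**2. One patient under three readings**

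Stop at week 10, stable at the safety scan, progression at week 16:

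- *Sections 5.2 and 5.7, 12-weekly:* first seen at week 26.3; success.
- *Section 5.5 with the 90-day definition in section 5.2:* on treatment to 10 + 90/7 = week 22.9, so the week-16 scan is due; failure. For stops from 24 − 12.9 = week 11.1 the week-24 scan is covered too.
- *Section 8.2.1:* scans at weeks 16 and 24; failure.

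**3. The plan's own figure**

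Cohort H (section 10.1.3) continues if at least 4 of 13 are progression-free and succeeds if at least 13 of 43 are. The success probability is

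Σ (x = 4 to 13) C(13,x) p^x (1−p)^(13−x) · P(Bin(30,p) ≥ 13 − x).

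This gives 0.0496 at p = 0.20 and 0.800 at p = 0.40, reproducing the stated 5% and 80%.

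**4. Sensitivity of cohort H**

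Assumptions, none from the documents: exponential progression at the 20% null; exponential stopping independent of progression; no deaths; no new therapy; scans at the 12-weekly visits; a share q stopping before week 24 without recorded progression. In simulation under the 12-weekly reading, about 45% of stoppers score as successes and about 30% are truly progression-free at week 24. About 40% of stoppers fall in the exposed window. The apparent null rate is roughly 0.20 + q(0.45 − 0.30): about 0.209, 0.220 and 0.230 for q = 6%, 13% and 20%. Putting the simulated rates into the formula in step 3 gives the one-sided error:

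| q | 12-weekly | 8-weekly to 90 days | Section 8.2.1 governs |
|---|---|---|---|
| 6% | 6.8% | 5.6% | 5.0% |
| 13% | 9.0% | 6.5% | 5.0% |
| 20% | 11.7% | 7.5% | 5.0% |

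**5. Adding new therapy to the 12-weekly reading**

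Suppose one third of stoppers start another therapy before week 24 and count as non-successes. The error is then about 5.0% at all three values of q. With one half it is about 4.2%, 3.5% and 2.8%.

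**The case against.** The best defence is that the protocol already provides the scans. Section 8.2.1 is not limited to treatment, and the 90-day definition in section 5.2 can carry the 8-weekly scans of section 5.5 past the last dose. This stands to the extent that the 12-weekly gap cannot be called settled, and the week-10 example fails under either alternative. It does not remove the problem. Sections 5.2 and 5.7 deal with exactly these patients and say 12 weeks, and the contact at 90 days may be a telephone call. A site cannot tell which text governs.

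The exposed group is also narrow. Sections 7.6.1 and 7.6.2 allow one drug to continue alone, so the patient must have stopped both. The stop must fall at about weeks 8 to 20, with progression after the safety scan and before week 24. A reader might infer that early stoppers in general are misread, but those who stop before about week 7.7 have a visit by week 24.

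A reader might also infer that ending follow-up at new therapy inflates the rate. The documents do not support that. If follow-up ends before week 24, no later progression is recorded, stable disease cannot exceed 24 weeks, and the patient remains in the denominator as a non-success. Only an earlier complete or partial response leaves the wording open, because the duration condition attaches to stable disease.

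The sensitivity figures leave out deaths and clinical progression, both of which would add failures. They also assume imaging at the 12-weekly visits, which sections 5.2 and 5.7 do not name.

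Finally, the SAP, which is not shown, may say how a missing week-24 status is scored. It cannot supply a scan that the protocol did not schedule.

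**Conclusion.** The protocol is inconsistent about tumour assessment after a stop without progression. One of its readings lets progression before week 24 count as a 6-month PFR success in cohorts B, H, I, M, N, O and P. The timing window of about weeks 8 to 20 follows from the protocol's own intervals.

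The size and net direction of any bias do not follow from the documents. The rise in cohort H's error to about 7-12% holds only under the 12-weekly reading with assumed stopping of 6-20%, no deaths and no new therapy. It shrinks to 5.6-7.5% under the 90-day reading, vanishes under section 8.2.1, and can be offset or reversed by new therapy. A reader should not take 7-12% as the trial's error rate. The point is worth acting on because the ambiguity concerns a primary endpoint and is cheap to remove.

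**What to change.** Reconcile sections 5.2, 5.5, 5.6, 5.7, 8.2.1 and 8.2.2.1. State once that tumour assessments and their central review stay on the calendar from cycle 1 day 1 (weeks 8, 16 and 24) until progression or week 24, whether or not study drug has stopped or another therapy has started. Begin 12-weekly follow-up only after that, and say whether those visits include imaging. In the same edit, align the 6-monthly follow-up in section 5.7, which is stated for all patients after discontinuation, with section 5.2, which limits it to those who have progressed or started new therapy.

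How to score patients who start new therapy before week 24 may be set in the SAP.

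Sample sizes and decision boundaries do not change; cohort H keeps 43 patients, error 0.0496 and power 0.800. The cost is a short amendment, at most about one extra CT in a few early stoppers, and possibly a slightly lower reported PFR.
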